## Abstract

**Background::**

Varicose veins of the lower extremities are common chronic venous diseases in the clinic. Although Western medicine has various surgical methods to treat varicose veins in the lower extremities, there are still a variety of complications. Some studies have shown that Buyang Huanwu decoction treatment of varicose veins of the lower extremities has a certain effect, and can reduce the occurrence of postoperative complications, but there is no evidence of evidence-based medicine. The research carried out in this scheme is to systematically evaluate the efficacy and safety of Buyang Huanwu decoction in the treatment of varicose veins in the lower extremities, and to provide reliable evidence for guiding clinical practice.

**Methods::**

This is a randomized, double-blind, placebo-controlled, parallel-group clinical trial, which studies the effectiveness and safety of Buyang Huanwu decoction in the treatment of varicose veins of the lower extremities. The patients are randomly and evenly divided into treatment group and control group, the former one is given Buyang Huanwu decoction and the latter one is given placebo. The study will last 49 days, including a 7-day washout period, 14-day intervention and 28-day follow-up, focusing on its efficacy and safety indicators. Observation indicators include: TCM syndrome score, Venous Clinical Severity Score (VCSS), Venous Disability Scote (VDS), Aberdeen Varicose Vein Questionnaire (AVVQ), Hemorheology Indicators, Adverse Reactions, etc. Data analysis is performed using SPSS 25.0 software.

**Discussion::**

This study will evaluate the effectiveness and safety of Buyang Huanwu decoction and provide clinical evidence for the treatment of varicose veins of the lower extremities.

**Trial registration::**

OSF Registration number: DOI 10.17605/OSF.IO/WGJXT.

## Introduction

1

Varicose veins (VVs) of the lower extremities are common chronic peripheral vascular diseases with incidences of 20% to 30%. The incidence of varicose veins in females is higher than that in males. The most common lesion was the great saphenous vein.^[1]^ The disease has a long course and can easily cause many complications such as chronic ulcer, thrombophlebitis, and vein rupture.^[2]^ Patients may have lower limb edema, pigmentation, deformity, bleeding, and other symptoms, which seriously affect the quality of their lives.^[3]^ Studies have shown that people who are engaged in manual work, especially standing work, are more likely to have varicose veins of the lower limbs.^[4]^ To date great progress has been made in the study of the pathogenesis of varicose veins of the lower extremities, which is closely related to vascular smooth muscle cells (VSMCs). Apoptosis, proliferation, and vascular remodeling of vascular smooth muscle cells can affect the veins of the lower extremities.^[5–7]^ For a long time, the traditional surgical treatment is high ligation of the junction of the great saphenous femur and exfoliation of the great saphenous vein, which is considered to be the gold standard of treatment.^[8]^ Although there are various surgical methods for the treatment of varicose veins of the lower extremities, they cannot effectively avoid postoperative limb swelling, subcutaneous hematoma, ecchymosis, saphenous nerve injury, and other complications, which brings inconvenience to the postoperative recovery of patients.^[9,10]^ Various postoperative complications not only affect limb movement, leading to delayed wound healing, but also cause psychological burden to patients, so it is particularly important to find other methods to treat or prevent the occurrence of postoperative complications.

Varicose veins of the lower extremities belong to the category of “muscle tumor” in Chinese medicine, and the pathogenesis is blood stasis as the core. In recent years, clinical studies have found that Chinese medicine plays an important role in the treatment of varicose veins of the lower extremities and the prevention of postoperative complications, which is conducive to the recovery of the disease and shortens the length of hospitalization.^[11]^ Buyang Huanwu decoction comes from *Correction on Errors in Medical Classics*. Its prescriptions are composed of Radix Astragali seu Hedysari, Lumbricus, Flos Carthami, Radix Paeoniae Rubra, Radix Angelicae Sinensis, Semen Persicae, and Rhizoma Ligustici Chuanxiong, aiming at invigorating vital energy and promoting blood circulation for removing obstruction in collaterals. Buyang Huanwu decoction can regulate lipid metabolism, stabilize plaque, and has a good effect on preventing atherosclerosis.^[12]^ With acupuncture and moxibustion treatment, it can well improve the clinical symptoms of patients with stroke sequelae.^[13]^ At the same time, Buyang Huanwu decoction has little clinical adverse effects. Therefore, we plan to evaluate the effectiveness and safety of Buyang Huanwu decoction through this randomized controlled trial, and provide a treatment plan for clinical treatment of varicose veins of the lower extremities.

## Materials and methods

2

### Study design

2.1

This is a randomized, double-blind, placebo-controlled, parallel-group clinical trial that indicates to study the effectiveness and safety of Buyang Huanwu decoction in the treatment of varicose veins of the lower extremities. The whole experiment will follow the comprehensive test report standard. And the flowchart is shown in Figure 1.

**Figure 1 F1:**
[figure not shown]
Flow diagram.

### Ethics and registration

2.2

This research protocol complies with the Declaration of Helsinki. Furthermore, it is approved by the clinical research ethics committee of our hospital and registered on OSF (registration number: DOI 10.17605/OSF.IO/WGJXT). Before randomization, all patients need to sign a written informed consent and they are free to choose whether to continue the trial at any time.

### Patients

2.3

Inclusion criteria: ①Meet the diagnostic criteria of western medicine for varicose veins of the lower extremities;^[14]^②People age between 20 and 70; ③All patients signed informed consent, and the research materials are complete.

Exclusion criteria: ①Those with insufficiency of important organs such as liver, kidney, heart and lung; ②Those suffer from other serious diseases such as malignant tumors; ③Those with severe mental illness; ④Those with deep vein thrombosis; ⑤Patients with allergies or contraindications to the medication used in this study; ⑥Patients who are unable to understand the research plan after explanation or unwilling to participate.

Exit criteria: ①Those who have serious adverse events or serious complications are not suitable for the next test; ②Those who have poor compliance and affect the judgment of effectiveness and safety; ③For any reason, the subject asked to withdraw from the trial.

### Sample Size Calculation

2.4

This study is a pilot clinical trial. Based on the analysis and calculation of the relevant literature published in the past 10 years, the efficiency of western medicine is 75.47%, and the effective rate of Chinese medicine combined with western medicine is 96.23%. The sample content estimation formula is used for comparison of multiple sample rates. Set the significance test level α = 0.05, then μ_α_ = 1.96, 1-β = 0.9, μ_β_ = 1.28, δ = π1-π2. The sample content estimation formula for comparing 2 sample rates: $N_{1}=N_{2}={\left(\frac{\mu_{\alpha }+\mu_{\beta }}{\delta }\right)}^{2}[\pi_{1}(1-\pi_{1})+\pi_{2}(1-\pi_{2})]$

The calculated sample size of each group is 54 cases. Considering factors such as shedding, it is expanded by about 20%, and 130 patients need to be included. According to the order of visits, the random number method was used to divide the patients into a control group and an observation group, with 65 cases in each group.

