### Study design

2.5

This study will recruit patients who come to the outpatient clinic to screen and happen to meet the criteria. The patients and their families will approve the study plan and sign an informed consent form. The patients are randomly assigned to the treatment group and the control group. Among them, the treatment group is given Buyang Huanwu decoction (Radix Astragali seu Hedysari 30 g, Lumbricus 6 g, Flos Carthami 6 g, Radix Paeoniae Rubra 10 g, Radix Angelicae Sinensis 10 g, Semen Persicae 6 g, and Rhizoma Ligustici Chuanxiong 6 g), 1 bag at a time (180 ml), twice a day; The control group is given a placebo. The packaging, color, taste, dosage form and size of the placebo are exactly the same as the treatment group. The 2 groups of patients will receive the same routine care and basic treatment, control the patient's blood sugar, blood pressure, blood lipids, etc., and receive health education. If necessary, the attending doctor can adjust the plan according to the patient's condition. All intervention methods will be recorded in detail. Used for final result analysis.^[15]^ We will set up a dedicated drug administrator, and the nurse will be responsible for preparing drugs. Therefore, this study is not blind to nurses, but to researchers, patients and statisticians. All patients will receive 14 days of treatment. Before and after treatment and on the 7th day of treatment, the health status of each patient will be assessed, including efficacy indicators and safety indicators, and all patients will be followed up for 28 days by telephone. Follow-up content includes cardiovascular events and rehospitalization.

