### Evaluation criteria and judgment of curative effect

2.6

1.Main observation indicators: Venous Clinical Severity Score; Venous Dysfunction Score^[16]^; TCM Syndrome Points;2.Secondary observation indicators: Aberdeen Varicose Vein Questionnaire; Hemorheology indicators (including whole blood viscosity, plasma viscosity, hematocrit, fibrinogen and erythrocyte sedimentation rate (ESR));3.Adverse reactions: Including abnormal liver function and any uncomfortable symptoms (such as dizziness, nausea, etc.) during treatment.

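### The stated 90% power is calculated for an effective rate that the trial does not list as an outcome, so it is not established for any of the three main scores

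*Protocol article*

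**What the plan says.** Section 2.4 takes its planning effect from published literature: "the efficiency of western medicine is 75.47%, and the effective rate of Chinese medicine combined with western medicine is 96.23" per cent. It then applies the formula for comparing two rates with these settings: "Set the significance test level α = 0.05", a normal quantile of 1.96 (so two-sided), and "1-β = 0.9, μ_β_ = 1.28". The result is given as "The calculated sample size of each group is 54 cases". For losses, "it is expanded by about 20%, and 130 patients need to be included", "with 65 cases in each group".

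Section 2.6 gives the outcomes: "Main observation indicators: Venous Clinical Severity Score; Venous Dysfunction Score^[16]^; TCM Syndrome Points". Secondary indicators are the Aberdeen questionnaire and hemorheology, followed by adverse reactions. No effective rate, responder definition or cut-off appears there or elsewhere in the article.

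Section 2.5 describes the comparison. One group receives the decoction; for the other, "The control group is given a placebo". Both groups receive the same routine care, described as control of blood sugar, blood pressure and lipids plus health education.

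Section 2.8 plans a two-group t test for measurement data, a rank sum test where normality fails, and a chi-squared test for counts.

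**The concern.** A stated power is tied to one outcome, one contrast and one assumed effect. Here the outcome used in the calculation is a proportion that is not in the outcome list, while the listed main outcomes are scores compared by their means or ranks. A 20.76-point difference in a response rate says nothing definite about the size of a difference in VCSS, because the article gives no rule linking the two.

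The source of the rates adds a second, narrower doubt. The 75.47% comes from patients on western medicine. The background care described in section 2.5 is risk-factor control and education, and no western treatment for varicose veins is named.

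What is at stake is how the result is read. If VCSS shows no significant difference, the report could say that a trial with 90% power found nothing. The plan gives no basis for that sentence.

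**Working it through.** **Step 1. Reproduce the plan's figure.** Inputs from section 2.4: rates 0.7547 and 0.9623, quantiles 1.96 and 1.28.

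- Difference: 0.9623 − 0.7547 = 0.2076
- Variance term: 0.7547 × 0.2453 + 0.9623 × 0.0377 = 0.1851 + 0.0363 = 0.2214
- n per group = ((1.96 + 1.28) / 0.2076)² × 0.2214 = 243.58 × 0.2214 = 53.93, rounded up to 54
- Allowance for losses: 54 × 1.2 = 64.8, so 65 per group and 130 in total

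The arithmetic agrees with the plan. The difficulty lies in which outcome was powered.

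**Step 2. Compare the powered outcome with the listed outcomes.**

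| | Section 2.4 | Sections 2.5, 2.6 and 2.8 |
|---|---|---|
| Outcome | Effective rate (binary) | VCSS, Venous Dysfunction Score, TCM syndrome points |
| Comparison method | Two proportions | t test or rank sum test |
| Contrast | Western medicine v Chinese plus western medicine | Placebo plus routine care v decoction plus routine care |
| Planning effect | 75.47% v 96.23% | No difference or SD given |

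**Step 3. What 54 or 65 per arm gives for a score.** The documents give no difference and no SD, so the standardised mean difference (SMD, difference divided by SD) is an assumed range. The setting is two-sided 0.05, a two-sample t test and equal groups.

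| Assumed SMD | Power, 54 per arm | Power, 65 per arm |
|---|---|---|
| 0.3 | 34% | 40% |
| 0.4 | 54% | 62% |
| 0.5 | 73% | 81% |
| 0.6 | 87% | 92% |

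**Step 4. SMD needed for a given power.** The normal approximation is SMD = (z for alpha + z for power) × √(2/n).

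- 54 per arm, 90%: (1.960 + 1.282) × √(2/54) = 3.242 × 0.1925 = 0.62; the t test gives 0.63
- 54 per arm, 80%: (1.960 + 0.842) × 0.1925 = 0.54; the t test also gives 0.54
- 65 per arm, 90%: 3.242 × √(2/65) = 3.242 × 0.1754 = 0.57; the t test also gives 0.57

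**Step 5. If all three scores are tested.** With an equal split of alpha, 0.05/3 = 0.0167 each (an assumption, since the article states no rule), the two-sided quantile is 2.394. The SMD for 90% power on a given score is then (2.394 + 1.282) × 0.1925 = 0.71 at 54 per arm, and 3.676 × 0.1754 = 0.64 at 65 per arm, by the normal approximation.

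**The case against.** Several things can be said for the plan, and some of them limit the point.

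*The true power may be adequate.* A reader might infer that the trial is underpowered for all three scores. The documents do not support that. With no difference or SD given, power on the scores is unknown. It is 90% or more if the true SMD is at least 0.63 with 54 evaluable per arm, or 0.57 with 65. This stands, and the conclusion has to be that the 90% is not established.

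*The contrast is not foreign to the trial.* A reader might infer that the planning rates come from a comparison the trial does not make. That goes too far. Decoction or placebo on top of common care is an add-on design, as is Chinese plus western medicine against western medicine. What remains is that the common care in section 2.5 is not shown to be the treatment that gave 75.47%.

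*The source of the rates.* The percentages match 40/53 and 51/53, and a reader might infer a single small study. Multiples such as 80/106 and 102/106 fit equally well, and section 2.4 refers only to literature of the past 10 years. The size of the source cannot be known from the article, and nothing here depends on it.

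*The study is called a pilot.* Section 2.4 does say so, but it also sets a formal power of 0.9 and alpha of 0.05. The Discussion says the trial is meant to verify a significant improvement in symptoms. The label does not cancel a stated power.

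*A condensed article may omit a responder definition.* The heading of section 2.6 speaks of judging curative effect, and the chi-squared test could analyse a response rate. That is possible, but section 2.6 sets out its indicators and no rate is among them. The problem is a conflict between two things the article does state. Had a responder outcome been intended, it would need listing and defining, and its rates would need justifying under placebo plus routine care.

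**Conclusion.** The concern holds in this form: section 2.4 attaches 90% power to an effective rate that is not among the trial's outcomes, so the figure is not established for VCSS, the Venous Dysfunction Score or the TCM syndrome points. The sample size arithmetic is right. The 75.47% control rate is, in addition, not shown to apply to the placebo arm.

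The size of the gap depends on an effect the documents do not give. Over assumed SMDs from 0.3 to 0.6, power with 54 evaluable per arm runs from 34% to 87%. These figures assume a two-sample t test at two-sided 0.05 on one score. They do not show that the trial falls short; they show how far the answer depends on a value the plan has not stated.

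**What to change.** Keep 130 patients and rewrite section 2.4:

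1. Remove the 90% claim based on the effective rate.
2. Name one of the three scores in section 2.6 as primary, or keep all three and state a multiplicity rule.
3. For one primary score at two-sided 0.05, state that 54 evaluable per arm gives 90% power for an SMD of 0.63 and 80% for an SMD of 0.54, and add the short power table for SMDs of 0.3 to 0.6.
4. If all three scores are tested, restate these figures at the alpha the rule gives each score. Under an equal three-way split, the SMD for 90% power is about 0.71 at 54 per arm.
5. Translate the SMD into score points once a source for the SD is cited.

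The cost is wording in the protocol and the registration, plus the decision on the primary score. No patients are added. The downside is that the stated power will look less favourable than the present 90%.

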### Study design

2.5

This study will recruit patients who come to the outpatient clinic to screen and happen to meet the criteria. The patients and their families will approve the study plan and sign an informed consent form. The patients are randomly assigned to the treatment group and the control group. Among them, the treatment group is given Buyang Huanwu decoction (Radix Astragali seu Hedysari 30 g, Lumbricus 6 g, Flos Carthami 6 g, Radix Paeoniae Rubra 10 g, Radix Angelicae Sinensis 10 g, Semen Persicae 6 g, and Rhizoma Ligustici Chuanxiong 6 g), 1 bag at a time (180 ml), twice a day; The control group is given a placebo. The packaging, color, taste, dosage form and size of the placebo are exactly the same as the treatment group. The 2 groups of patients will receive the same routine care and basic treatment, control the patient's blood sugar, blood pressure, blood lipids, etc., and receive health education. If necessary, the attending doctor can adjust the plan according to the patient's condition. All intervention methods will be recorded in detail. Used for final result analysis.^[15]^ We will set up a dedicated drug administrator, and the nurse will be responsible for preparing drugs. Therefore, this study is not blind to nurses, but to researchers, patients and statisticians. All patients will receive 14 days of treatment. Before and after treatment and on the 7th day of treatment, the health status of each patient will be assessed, including efficacy indicators and safety indicators, and all patients will be followed up for 28 days by telephone. Follow-up content includes cardiovascular events and rehospitalization.

### Evaluation criteria and judgment of curative effect

2.6

1.Main observation indicators: Venous Clinical Severity Score; Venous Dysfunction Score^[16]^; TCM Syndrome Points;2.Secondary observation indicators: Aberdeen Varicose Vein Questionnaire; Hemorheology indicators (including whole blood viscosity, plasma viscosity, hematocrit, fibrinogen and erythrocyte sedimentation rate (ESR));3.Adverse reactions: Including abnormal liver function and any uncomfortable symptoms (such as dizziness, nausea, etc.) during treatment.

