### Data collection and management

2.7

Before the start of treatment, 7 days after the start of the treatment, and at the end of the treatment, collect data according to the evaluation criteria. 28 days after the end of the treatment, each patient will be followed up by outpatient or telephone. The detailed record of the follow-up information cannot be collected. Two assistants cooperate to collect. Personal information about potential participants and registered participants will be collected, shared and stored in an independent storage room to protect confidentiality before, during and after the test. Access to the database is limited to researchers in this research group.

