### Statistical analysis

2.8

In this study, SPSS25.0 statistical analysis software is used for data analysis, and the measurement data is represented by ($\bar{x}\pm s$); For data conforming to normality and homogeneity of variance, the group *t* test is used between groups, and the paired *t* test is used within the group; the rank sum test is used for those that does not conform to the normal distribution; the Chi-Squared test is used for count data. *P* < .05 is statistically significant.

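### Three unranked main scores, assessed at two visits and tested at an unadjusted .05, push the false-positive risk above 5% if any one score may carry the efficacy claim

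*Protocol article*

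**What the plan says.** - **Outcomes (section 2.6).** "Main observation indicators: Venous Clinical Severity Score; Venous Dysfunction Score^[16]^; TCM Syndrome Points". No score is ranked above the others. Listing order does not help: section 2.6 puts the TCM score last among the three, while the abstract's Methods paragraph puts it first.
- **Visits (sections 2.5 and 2.7).** Section 2.7 reads "Before the start of treatment, 7 days after the start of the treatment, and at the end of the treatment, collect data". Section 2.5 agrees: "Before and after treatment and on the 7th day of treatment, the health status of each patient will be assessed, including efficacy indicators and safety". That makes two post-baseline assessments, and neither is named as the main one. The 28-day follow-up adds no third score visit on its face: "Follow-up content includes cardiovascular events and rehospitalization".
- **Tests (section 2.8).** "the group *t* test is used between groups, and the paired *t* test is used within the group", with a rank sum test where normality fails. The threshold is a single P value: "< .05 is statistically significant". No adjustment, test order or all-must-succeed rule accompanies it.
- **Sample size (section 2.4).** One alpha of 0.05 and 90% power are applied to an effective rate of 75.47% versus 96.23%. That variable does not appear among the indicators in section 2.6.

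**The concern.** Three main scores at two post-baseline visits give up to six between-group comparisons, each judged at .05. With no ranking and no main time, a significant difference on any one of them could be reported as efficacy on a main outcome. The error rate of such a claim would be higher than the 5% set in section 2.4.

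The sample size calculation would normally show which endpoint carries the claim. Here it does not, because it uses a variable outside the list of main indicators. If the score and visit are picked after the results are seen, error control cannot be restored.

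**Working it through.** **1. Reproduce the plan's own figure.** Inputs from section 2.4: π1 = 0.7547, π2 = 0.9623, z values 1.96 and 1.28.

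- δ = 0.9623 − 0.7547 = 0.2076
- Variance term: 0.7547 × 0.2453 + 0.9623 × 0.0377 = 0.1851 + 0.0363 = 0.2214
- N per group = (3.24 / 0.2076)² × 0.2214 = 53.93, rounded up to 54. This matches the article.
- 54 × 1.2 = 64.8, rounded to 65 per group and 130 in total. This also matches.

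The arithmetic is sound, but it describes one two-sided test at 0.05 of an effective rate. It identifies none of the three scores as primary.

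**2. Count the tests.** Three main scores (section 2.6) at one visit give 3 tests. At day 7 and end of treatment (sections 2.5 and 2.7) they give 3 × 2 = 6. The count leaves out the secondary indicators and the within-group paired tests.

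**3. Chance of at least one false positive, independent tests.** The formula is 1 − (1 − 0.05)^k.

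- k = 3: 1 − 0.95³ = 0.143
- k = 6: 1 − 0.95⁶ = 0.265

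**4. Correlated tests.** The article gives no correlations, so these are assumed. Multivariate normal test statistics with a common correlation were simulated (1,000,000 draws), each tested two-sided at 0.05.

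| Assumed correlation | 3 tests (one visit) | 6 tests (both visits) |
|---|---|---|
| 0 | 14.3% | 26.5% |
| 0.5 | 12.6% | 20.7% |
| 0.7 | 10.9% | 16.4% |
| 0.9 | 8.4% | 10.8% |
| 0.95 | 7.4% | 8.9% |

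The picture is similar when scores and visits are given separate correlations. With 0.5 between scores and 0.7 between visits, six tests give 20.3%. With 0.8 and 0.9 they give 13.5%.

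**5. Effect of a correction.** Holm across the three end-of-treatment tests compares the smallest P value with 0.05/3 = 0.0167, the next with 0.05/2 = 0.025 and the last with 0.05, stopping at the first failure. This holds the overall rate at or below 5% whatever the correlation. One score at one time, tested at 0.05, gives 5% directly.

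**The case against.** **The claim rule is inferred.** Section 2.8 says when a test is called significant. It does not say that one significant score at one visit establishes efficacy, and section 2.7 is a collection schedule that does not make day 7 a confirmatory comparison. If all three scores had to succeed at a fixed visit, there would be no inflation. This objection stands, and it makes every figure above conditional. It does not remove the point, because the article states no all-must-succeed rule either and leaves the any-one reading open.

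**The article is condensed.** A multiplicity procedure could sit in a full protocol or analysis plan that is not shown. That also stands, so the point is not that no such procedure exists anywhere. The point is what this article itself fixes: three co-equal main outcomes with an unadjusted .05. Which outcome and time carry the claim is a design decision, not an analysis detail.

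**The scores are related and measured a week apart in the same patients.** Independence is therefore an unlikely ceiling. Even so, no correlation examined brings the rate down to 5%.

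**The trial is called a pilot.** Section 2.4 uses that word, yet it powers a hypothesis test at 90%, and the Discussion gives verification of a significant improvement in symptoms as the aim. The label does not settle the matter.

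**Stronger readings that a reader might infer.** One is that the trial's false-positive rate simply is some figure in the range above. The documents do not support that, because the size depends on assumed correlations, on the number of visits counted and on the any-one reading. Another is that there is no primary endpoint at all. That is also wrong: three main indicators are named, and what is missing is a single one or a rule for combining them.

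**Conclusion.** The point holds in conditional form. The article names three unranked main scores and two post-baseline visits, and it applies an unadjusted .05 throughout. If any one significant main score supports an efficacy claim, the chance of at least one false positive is 14.3% to 8.4% for three tests at one visit, and 26.5% to 10.8% for six tests over both visits, as the assumed correlation goes from 0 to 0.9. Above 0.9 it falls further (7.4% and 8.9% at 0.95) but stays over 5%.

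The textual facts are firm. The size rests on correlations that the article does not supply and on a success rule that it permits without stating.

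**What to change.** In sections 2.6 and 2.8, make the end of the 14-day treatment the primary time and label day 7 as supportive. Then adopt one of two rules:

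1. Keep all three main scores and test them with Holm at an overall two-sided 0.05.
2. Before unblinding, have the sponsor name one score as the single primary endpoint, tested two-sided at 0.05, and test the other two in a stated fixed sequence.

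The choice of score under option 2 belongs to the sponsor. Position in a list is no basis for it, since the abstract and section 2.6 list the scores in different orders.

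**Cost.** About one paragraph of text and an update of the registration. Holm takes some power from each score. With a single primary endpoint, another score can no longer carry the efficacy claim alone. Section 2.4 also needs a sentence: its 90% power belongs to the effective rate and should not be claimed for any of the three scores unless a calculation for the chosen endpoint is added.
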